##### High Dose Rate (HDR) Brachytherapy

Total HDR brachytherapy dose to Point A will be 24-30 Gy: in 6-8 Gy fractions delivered in 3-5 weekly HDR brachytherapy procedures to deliver an LDR equivalent dose of 40 Gy. HDR brachytherapy should start week 3-5. When HDR brachytherapy begins, at least one insertion will be performed per week with no external beam therapy given on the day of the insertion. If the majority of the external beam radiation has been given, then two insertions per week could be done separated by at least 72 hours in order to complete all treatment with 8 weeks.

##### Brachytherapy Instruments

It is recommended that tandem and ovoids or tandem and ring be used for HDR brachytherapy, and tandem and ovoids or tandem alone for LDR/PDR brachytherapy. Image-guided brachytherapy will be permitted.

##### Determination of Normal Tissue Tolerance

In order to stay below an LDR equivalent of 70 Gy to the rectum (120 Gy) for the 3-5 HDR insertions, including the 45-50 Gy contribution from the external beam radiation, the rectum should receive less than 4.1 Gy for each HDR fraction of 6 Gy (68% of the prescribed dose to Point A). The dose to the bladder should be less than 4.6 Gy per each HDR fraction of 6

Gy (77% of the prescribed dose to Point A). As in LDR brachytherapy, every attempt should be made to deliver tumouricidal doses, even if the late responding tissues receive a slightly higher dose. Brachytherapy volumes and doses will be compared between the two intervention groups.

## **8.2. Standard Chemotherapy for Locally Advanced Cervical Cancer**

Cisplatin 40 mg/m^2 (max 70 mg) IV given weekly for a total of six weekly cycles.

## **9. CONCOMITANT MEDICATION**

### **9.1. Prohibited Concomitant Medication and Therapy**

Aminoglycoside antibiotics (see *Appendix VIII*) given before, with or after cisplatin may potentiate renal toxicity and should be avoided whenever possible.

## **10. EVALUATION DURING AND AFTER TREATMENT**

*Refer to Appendix III: Schedule of Study Assessments and Evaluations*

### **10.1. Treatment Period Assessment**

The usual practice at Ontario centres is for patients to undergo weekly blood tests (CBC plus differential, creatinine, and electrolytes) during chemo-RT treatment. However, the blood tests and their frequency will be left to the discretion of the local investigators.

### **10.2. Follow-up Assessment**

Patient follow-up care will be at the discretion of the investigator at the local site. It is suggested that follow-up care be in accordance with the Cancer Care Ontario guidelines. For the purposes of collection of study related data, patients will be followed for approximately 5 years. Assessments will be calculated from the date of randomization.

Patients will be assessed every 6 months ( $\pm 14$  days) for the first 2 years (Year 1 and 2). At each follow-up visit, patients will be required to return to the clinic to assess current disease status. ECOG performance status will also be assessed and documented. The two QoL questionnaires (EORTC QLQ-30 version 3 and QLQ-CX24) will be completed by the patient at 3, 6, 12, 18 and 24 months after randomization. These questionnaires can be either mailed to the patient or completed by the patient at a clinic visit (see *Appendix IV*).

To perform the health economic evaluation, a limited set of questions on health care resource utilization and patient utility will be incorporated into the data collection. The health utility questionnaire (EQ-5D) will be completed by the patient at 3, 6, 12, 18 and 24 months after randomization. This questionnaire can be either mailed to the patient or completed by the patient at a clinic visit (see *Appendix V*).

Information on a patient's cancer status (free of disease or not) and overall survival will be abstracted from their cancer centre or hospital records, or by contacting the family physician at least once a year for Years 3, 4, and 5.

On completion of the 5 years of follow-up required by this study, further assessment of the patient will be according to the oncologist's or local institutional practice; patients will not be restaged at the end of the 5-year follow-up period.

## 11. ADVERSE EVENTS

This study will be conducted in accordance with Health Canada regulatory requirements and ICH Good Clinical Practice guidelines. Adverse events (AEs) and Serious Adverse Events (SAEs) data will be reported and collected.

### 11.1. Adverse Event Definitions

An **Adverse Event (AE)** is defined as any untoward medical occurrence in a patient who is administered a drug or biologic (medicinal product) or using a medical device; the event does not necessarily have a causal relationship with this treatment. An AE can therefore be any unfavourable and unintended sign (including an abnormal laboratory finding), symptom, or disease temporally associated with the use of a medicinal (investigational) product, whether or not related to the medicinal (investigational) product. Each AE is to be classified by the Investigator as serious or non-serious.

A **Serious Adverse Event (SAE)** is any untoward medical occurrence that at any dose:

- results in death,
  - is life-threatening (i.e., immediate risk of death),
  - requires inpatient hospitalization or prolongation of existing hospitalization, except pre-planned hospitalizations required as part of a standard procedure or cancer treatment,
  - results in persistent or significant disability / incapacity,
  - is a congenital anomaly / birth defect
- OR
- is an important medical event, which is not immediately life threatening or requiring hospitalization, but may otherwise jeopardize the patient or may require intervention to prevent other outcomes specified in the above definition of SAE

An AE is **unexpected** when the nature or severity of the AE is not consistent with the applicable product information (i.e., Investigator's Brochure) for an unapproved investigational product or package insert/summary of product characteristics for an approved product. An AE is considered to be associated with the use of the drug if the attribution is classified as "Possible", "Probable" or "Very Likely".

## 11.2. Attribution Definitions

|             |                                                                                                                                                                                                                                                                                        |
|-------------|----------------------------------------------------------------------------------------------------------------------------------------------------------------------------------------------------------------------------------------------------------------------------------------|
| Not Related | An AE which is not related to the use of the study drug.                                                                                                                                                                                                                               |
| Doubtful    | An AE for which an alternative explanation is more likely (e.g. concomitant medication, concomitant disease), and/or the relation with time suggests that a causal relationship is unlikely.                                                                                           |
| Possible    | An AE which might be due to the use of the study drug. An alternative explanation (e.g., concomitant medication, concomitant disease) is inconclusive. The relationship in time is reasonable; therefore the causal relationship cannot be excluded.                                   |
| Probable    | An AE which might be due to the use of the study drug. The relationship in time is suggestive (e.g., confirmed by a de-challenge). An alternative explanation is less likely (e.g., concomitant medication, concomitant disease).                                                      |
| Very Likely | An AE, which is listed as a possible adverse reaction and cannot be reasonably explained by an alternative explanation (e.g., concomitant medications, concomitant diseases). The relationship in time is very suggestive (e.g. it is confirmed by a de-challenge and a re-challenge). |

## 11.3. Adverse Event Reporting Criteria

The investigational drug for this trial is  $^{18}\text{FDG}$ . Currently, all clinical trials involving  $^{18}\text{FDG}$  PET-CT require regulatory approval through Health Canada, hence, AEs and SAEs will be considered related to study drug if they are deemed to be related specifically to the administration of  $^{18}\text{FDG}$ . **Since all procedures other than that directly related to  $^{18}\text{FDG}$  PET-CT are standard of care, only AEs attributable to  $^{18}\text{FDG}$  will be collected.**

Progression of cancer and complications related to cancer treatment (e.g. surgery, chemotherapy and/or radiotherapy) are expected and bear no relationship to  $^{18}\text{FDG}$ , therefore they will not be documented as AEs or SAEs for the purpose of this trial. Deaths due to recurrent cancer are also expected and will not be reported as SAEs for the purpose of this trial. Deaths will be monitored by the Data Safety Monitoring Board.

AEs are to be recorded within the electronic CRF. Whenever possible, symptoms should be grouped as a single syndrome or diagnosis. The Investigator should specify the date of onset, grade, action taken with respect to Investigational Product, corrective treatment/therapy given, outcome and his/her opinion as to whether there is a reasonable possibility that the AE was related to the Investigational Product.

The severity of all AEs will be graded according to the NCI CTCAE, version 4.02. For each event, the highest severity grade attained since the last assessment period will be reported. If a CTCAE score does not exist, the Investigator should assess the event as Grade 1 (mild), Grade 2 (moderate), Grade 3 (severe), Grade 4 (life-threatening or disabling) or Grade 5 (causing death) to describe the maximum intensity of the AE.

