## 1.6. Upstaging and Treatment

When the pelvic nodes and para-aortic nodes are normal on imaging, patients receive pelvic RT (45-50 Gy by external beam to the level of L5/S1 plus brachytherapy) and weekly cisplatin-based chemotherapy. The detection of tumour in the common iliac or para-aortic nodes by an imaging test leads to a change in the RT volume of the combined modality treatment (suggested treatments indicated in Table 5). Patients receive pelvic RT and para-aortic RT (40-45 Gy) to include para-aortic nodes to the T12/L1 level. This RT is also referred to as extended field RT (EFRT). The addition of EFRT increases the side effects of treatment e.g. 3% major toxicity to the small bowel. If imaging detects disease in the common iliac nodes, the pelvic RT fields are altered to include the next echelon lower para-aortic nodes up to L1/L2. The detection of tumour in the pelvic nodes may also lead to a change in treatment with an increase in the pelvic RT field to the L4 level. Finally, if imaging detects distant disease e.g. supraclavicular or mediastinal nodes, bone, liver, or lung, the patient is no longer a candidate for combined modality chemo-RT and can receive symptom management and/or palliative care. In some cases, PET-CT may downstage nodes or metastatic sites thought to be involved on the basis of CT, resulting in less extensive treatment.

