#### 11.4. Adverse Event Reporting Period

The AE reporting period for this study begins at the time of administration of FDG and continues until 30 days after the administration of FDG or at death if it occurs earlier.

In addition, any known untoward event of Grade 3 or greater severity that occurs subsequent to the AE reporting period that the Investigator assesses as Possibly, Probably or Very Likely related to the administration of FDG should be reported as an SAE.

All AEs and SAEs must be followed until resolution unless, in the investigator's opinion, the condition is unlikely to resolve because of the subject's underlying disease.

Patients withdrawn from the study due to an AE will be followed until the AE has resolved. In the case of an SAE, the patient will be followed until clinical recovery or until progression has been stabilized or judged to be chronic.

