### **13.2. Sample Size and Feasibility**

It is postulated that approximately 25% of patients having the CT of the abdomen and pelvis alone will receive either palliative care (~10%) or EFRT (~15%). The use PET-CT in addition to CT of the abdomen and pelvis would be considered valuable if the proportion of patients treated with either palliative care or EFRT increased to 45% (20% and 25% respectively). These estimates are derived using the estimates available from the previous smaller studies performed on the older PET scanners. Further, a 20% absolute difference was felt to be a clinically important difference and is slightly more conservative than the 50% relative change in treatment rate observed in the OCOG trial of PET in early lung cancer. Based on these considerations, a trial with 288 patients (192 PET-CT, 96 CT abdomen and pelvis) will have over 90% power to detect a difference of this magnitude using the Fisher's exact test ( $\alpha=0.05$ , two-sided).

The 2:1 randomization for this trial allows us to gain additional understanding of the potential effect of FDG PET-CT plus CT of the abdomen and pelvis to CT of the abdomen and pelvis alone, which is currently the standard of care in patients with locally advanced cancer of the cervix. Using this unbalanced allocation will increase the number of patients who receive FDG PET-CT and could potentially help with recruitment. We feel this is ethical as preliminary data indicate the use of PET-CT may be better than CT abdomen and pelvis alone and it is unlikely that PET-CT will be detrimental to the individual patient. (Although unlikely to be detrimental, it is unclear that there is a benefit and even if a benefit exists, whether it is sufficient to warrant extensive use of PET-CT, hence the rationale for the study).

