### **13.6. Planned Interim Analysis**

One planned interim efficacy analysis will be performed after 50% of patients have been accrued. The Haybittle-Peto approach will be used, such that if the proportion of patients receiving standard pelvic chemo-radiation following CT abdomen and pelvis + PET-CT is significantly less (one-sided  $\alpha=0.001$ ) than the proportion of patients receiving standard pelvic chemo-radiation following CT abdomen and pelvis alone, then the Data Safety Monitoring Board (DSMB) will be expected to recommend to the Steering Committee that the trial should be discontinued early. In addition to the interim analysis based on efficacy, the DSMB will review accumulating safety data annually, starting approximately twelve months after study commencement. The Steering Committee will make the final decision about study continuation based on these recommendations.

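### Complications of chemo-radiotherapy are recorded as adverse events in neither arm, although PET-CT staging is expected to change treatment, so toxicity will be visible only indirectly

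*Protocol*

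**What the plan says.** Protocol section 11.3 names FDG as the investigational drug and limits collection to events attributable to it. It states "Progression of cancer and complications related to cancer treatment (e.g. surgery, chemotherapy and/or radiotherapy) are expected and bear no relationship to" FDG, and draws the consequence: "therefore they will not be documented as AEs or SAEs for the purpose of this trial". Deaths are monitored by the DSMB.

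Section 11.4 ties the window to the tracer: "The AE reporting period for this study begins at the time of administration of" FDG. It closes after 30 days, or at death if earlier. Later grade 3 or higher events count only if judged related to FDG. The schedule in Appendix III agrees: the AE/SAE row is marked at the study intervention, not in the treatment or follow-up columns.

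On the effect of the strategy, section 13.2 postulates that about 25% of CT-alone patients "will receive either palliative care (~10%) or EFRT (~15"%), and calls PET-CT valuable if the share "treated with either palliative care or EFRT increased to 45% (20% and 25% respectively"). On the toxicity of one of these treatments, section 1.6 says "The addition of EFRT increases the side effects of treatment e.g. 3% major toxicity to the small bowel".

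On monitoring, section 13.6 says "the DSMB will review accumulating safety data annually, starting approximately twelve months after study commencement".

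**The concern.** The exclusion rests on a relation to the tracer, but the tracer is not what the trial evaluates. Section 3 randomises two imaging strategies, and section 12.1 makes treatment delivered the primary outcome. If PET-CT works as planned, patients in the two arms will receive different treatments. Complications of those treatments are then a consequence of the randomised strategy, even though FDG does not cause them.

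Two things are at stake. First, the final report will have no graded toxicity rates by arm or by treatment category to set beside the change in treatment. Section 13.2 supports the 2:1 allocation partly with the view that "it is unlikely that PET-CT will be detrimental to the individual patient"; graded toxicity is one of the data needed to check that view. Second, the DSMB's information is uneven. Under section 13.6 a sufficiently large fall in standard pelvic chemo-radiation in the PET-CT arm is expected to lead to a recommendation to stop early. A move to EFRT counts towards that boundary, yet the only harm data the protocol gives the DSMB are deaths and FDG events, and FDG events can arise in one arm only.

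**Working it through.** **Design inputs.** From section 13.2: 192 PET-CT and 96 CT-alone patients; EFRT 25% against 15%; palliative care 20% against 10%. The plan's own figures reproduce. The continuity-corrected formula for 25% against 45% at 90% power gives 96 controls at 2:1 (96 + 192 = 288) and 128 per arm at 1:1. Exact two-sided Fisher power is 91.5% at 96/192. The point does not depend on the sample size, but these rates are used below.

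**Is any treatment toxicity collected elsewhere as an AE?** Sections 11.3 and 11.4 and Appendix III agree that it is not. The CT-alone arm receives no FDG and so has no AE window at all. Section 11.5 sets a 5-day limit for all other SAEs, but it cannot reopen what 11.3 excludes.

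**Expected shift in treatment**
- EFRT: 192 × 0.25 = 48 and 96 × 0.15 = 14.4. Excess in the PET-CT arm over the control rate: 192 × 0.10 = 19.2 courses.
- Palliative care: 192 × 0.20 = 38.4 and 96 × 0.10 = 9.6. Excess: 192 × 0.10 = 19.2 patients.

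Half of the assumed 20-point shift is towards EFRT and half is away from curative chemo-radiotherapy.

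**Expected small-bowel events from EFRT.** Events = arm size × EFRT rate × toxicity rate. The 3% is the protocol's, read here as the rate in EFRT patients; the other rates are assumptions to show the range.

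| Toxicity with EFRT | CT alone (96) | PET-CT (192) | Excess per 100 | Fisher power |
|---|---|---|---|---|
| 3% | 0.43 | 1.44 | 0.3 | 0.3% |
| 5% | 0.72 | 2.40 | 0.5 | 0.5% |
| 10% | 1.44 | 4.80 | 1.0 | 1.8% |
| 15% | 2.16 | 7.20 | 1.5 | 4.5% |

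At 3% the arm rates are 0.15 × 0.03 = 0.45% and 0.25 × 0.03 = 0.75%.

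**Net direction of all severe toxicity.** The protocol gives no figures for this. Assume a rate b with pelvic chemo-radiotherapy, b + i with EFRT, and none with palliative care:
- CT alone: 0.75b + 0.15(b + i) = 0.90b + 0.15i
- PET-CT: 0.55b + 0.25(b + i) = 0.80b + 0.25i
- Difference: 0.10(i − b)

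The sign depends on whether the EFRT increment exceeds the background rate. In percentage points:

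| b | i = 3 | i = 10 | i = 20 |
|---|---|---|---|
| 10% | −0.7 | 0.0 | +1.0 |
| 20% | −1.7 | −1.0 | 0.0 |
| 30% | −2.7 | −2.0 | −1.0 |

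Under these assumptions the arms could differ by −2.7 to +1.0 points, so the exclusion could hide a benefit of PET-CT as easily as a harm.

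**The case against.** The strongest reply is that toxicity is not unseen. The DSMB monitors deaths. EFS and OS count death from any cause (section 12.2). QLQ-C30 and QLQ-CX24, with diarrhea, bowel, bladder and vaginal items, are completed in both arms to 24 months. Section 13.4 compares quality of life between arms and also looks at it by treatment regimen. Appendix IX costs hospitalizations by arm and estimates QALYs.

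This stands, and it rules out two stronger readings. A reader might infer that neither the DSMB nor the final report can show any harm of the PET strategy; the sources just listed can show some. A reader might also infer that a rise in EFRT can only be read as a gain; worse quality of life, fewer QALYs or higher costs would count against it. But these are partial substitutes. The questionnaire items are ungraded and end at 24 months, and their analysis set needs a baseline and at least one follow-up form. Resource data are not graded or attributed to treatment, and Appendix IX limits further collection after recurrence. Apart from deaths, the protocol routes none of this to the DSMB.

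A third inference, that PET-CT makes treatment more toxic overall, is not supported either. Half the assumed shift is to palliative care, section 15 describes that as sparing a long non-curative course, and section 1.6 foresees downstaging.

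A reader might also combine the pooled PET accuracy of Table 3 with the nodal prevalence of Table 2 to count patients given EFRT on a false-positive scan. The documents do not support such a count. Three of the four para-aortic accuracy studies took patients with a prior negative CT or MRI, Table 2 covers only Stages II and III while the trial enrols IB to IVA, and there is no matching count for CT in the control arm.

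Finally, section 11.3 gives a reason: everything other than FDG PET-CT is standard care. That is a good reason not to report these events as FDG reactions or in expedited form. It is not a reason to leave them unrecorded as outcomes of a strategy that changes who gets which standard treatment.

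**Conclusion.** The point holds in this form: graded complications of chemo-radiotherapy are excluded from AE and SAE collection in both arms, on a ground that fits the tracer and not the staging strategy under test. Harm or benefit in toxicity will be visible only indirectly, and apart from deaths the DSMB is given no treatment toxicity by arm. This is not detail left to an analysis plan, because no plan can recover events that the protocol says are not to be documented.

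The demonstrable size is small. At the protocol's 3%, about 1.4 against 0.4 major small-bowel events are expected, a difference of 0.3 per 100 patients. That figure is only the protocol's example, and none is given for other toxicity. The net direction is open; the range of −2.7 to +1.0 points rests on assumed background and increment rates and on zero toxicity with palliative care. The data would support description and DSMB review, not a powered comparison. The change is worth making because it is cheap, but the trial's primary comparison does not depend on it.

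**What to change.** Keep the FDG rule in section 11.3 for expedited reporting. Add to section 11.3 and Appendix III:
- From randomization, in both arms, record gastrointestinal and genitourinary complications of study treatment of grade 3 or higher, using the CTCAE version already adopted, and treatment-related deaths, at the existing 6-monthly visits in Years 1 and 2.
- In Years 3 to 5, record only treatment-related deaths and late complications that led to hospitalization, as found at the annual record check.
- None of these needs expedited reporting.
- Tabulate them descriptively by randomised arm and by treatment category, for the annual DSMB review and the final report.

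Haematological grades are left out because section 10.1 leaves blood tests and their frequency to local discretion. Full grading in Years 3 to 5 is left out because section 10.2 relies then on records or the family physician. The wording of section 11.5 on all other SAEs should be reconciled with 11.3 at the same time.

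The cost is modest data entry at sites, with no added visits or procedures. Some acute events will be gathered retrospectively, because treatment is planned to finish within eight weeks and study visits are six months apart.
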